## Abstract

**Background:**

The latest scientific reports raise concerns about the rapidly increasing burden of chronic diseases in the state of Qatar. Pregnant Qatari women often confront complications during pregnancy including gestational diabetes, hypertension, abortion and stillbirth. The investigation of early life environmental, genetic, nutritional and social factors that may affect lifelong health is of great importance. Birth cohort studies offer a great opportunity to address early life hazards and their possible long lasting effects on health.

**Methods/design:**

The Qatari Birth Cohort study is the first mother-child cohort study in the Middle East Area that aims to assess the synergetic role of environmental exposure and genetic factors in the development of chronic disease and monitor woman and child health and/or obstetric characteristics with high prevalence. The present manuscript describes the recruitment phase of the study (duration: 2 years; expected number: 3000 families), where the pregnant Qatari women and their husbands are being contacted before the 15th week of gestation at the Primary Health Care Centers. The consented participants are interviewed to obtain information on several factors (sociodemographic characteristics, dietary habits, occupational/environmental exposure) and maternal characteristics are assessed based on anthropometric measurements, spirometry, and blood pressure. Pregnant women are invited to provide biological samples (blood and urine) in each trimester of their pregnancy, as well as cord blood at delivery. Fathers are also asked to provide biological samples.

**Discussion:**

The present study provides invaluable insights into a wide range of early life factors affecting human health. With a geographical focus on the Middle East, it will be a resource for information to the wider scientific community and will allow the formulation of effective policies with a primary focus on public health interventions for maternal and child health.

## Background

Early life events during critical developmental periods, may have significant impacts on the maintenance of lifelong healthiness. Recent epidemiological and experimental evidence points out how an adverse intrauterine environment, related to maternal dietary or placental insufficiency, could program susceptibility of the fetus to later development of cardiovascular or metabolic diseases such as obesity, hypertension, insulin resistance and type 2 diabetes [1, 2]. The ‘early life programming’ concept was originally proposed so as to explain the link between maternal nutritional deficits during pregnancy, low birth weight (less than 2.500 g) and risk for disease in lifespan [3]. This concept has been later expanded to the developmental origins of health and disease (DOHaD) model, which links fetal development to an unfavorable environment with the development of non-communicable diseases in later life [4, 5]. Psychiatric research has been inspired by the DOHaD model with a key focus being to provide insights into the etiology of mental disorders emerging from early life traits. Pregnancy and birth cohort studies provide the most suitable design to assess early life hazards at critical time points during development, and their possible long-lasting effects.

The rising incidence of chronic disease constitutes a major public health issue affecting many countries worldwide. In the Middle East, recent reports have raised this concern for member states of the Gulf Cooperative Council (GCC), where a higher burden of chronic diseases than most developed countries is observed [6–8]. The World Health Organization (WHO) Qatar STEPS survey of chronic disease risk factors in 2012 reported that almost half of the general Qatari population is at high risk for developing chronic diseases [9]. High prevalence rates of diabetes [10], cardiovascular disease [11], metabolic syndrome [12], hypertension [13], and mental illness have been reported in the population of Qatar [14]. Given the high levels of obesity and diabetes in Qatar, it is likely that a significant percentage of pregnancy complications will be associated with maternal obesity, type 2 diabetes and gestational diabetes. There is also a high concern on the increased incidence of mental disorders (such as postpartum depression, anxiety, and personality disorder) in Qatari women at the reproductive age [15].

In line with the increased incidence of chronic diseases in Qatar, there also exists a higher than expected prevalence of specific adverse birth outcomes such as stillbirths (6.9%), preterm births (8.5%) and low birth weight (8.8%) deliveries [16, 17]. Recent studies have reported that the impact of stillbirths on Qatar’s perinatal mortality has increased 17% within two decades [16], but with no sufficient data explaining this incidence. Moreover, gestational diabetes and gestational hypertension are the main complications observed in Qatari pregnant women [18].

Given the limited number of birth cohort studies in the Middle East, which mainly focus on specific health outcomes, the establishment of a mother-child cohort in Qatar is an excellent opportunity to address a broad range of research questions. The Qatari Birth Cohort Study (QBiC) aims to examine how environmental, genetic, nutritional and social factors affect health at first stages of life and childhood. The study focuses on the two most critical time windows of human development, the in utero exposure of the fetus through maternal exposures and the early life exposures as they are related to transgenerational alterations in ‘omic’ profile and disease onset. This project will comprise risk and benefit analyses including maternal and early life health monitoring as well as an extensive range of ‘omic’ analyses for the in depth investigation of the impact of genome-exposure synergy in the establishment of adverse birth outcomes and chronic diseases development. Moreover, the present study will investigate the increasing stillbirth rates [16, 17] and the concern of high abortion that was raised by the Permanent Population Committee at Qatar Population Status 2012 report [19]. The envisaged work has major potential for translational exploitation both national and international aiming to develop harmonized data for future collaborations with international birth cohorts. The purpose of the present protocol is to introduce the study design and the methods that are used for the recruitment phase of this longitudinal birth cohort in the state of Qatar.

## Methods/design

The QBiC study is the first mother-child cohort in the state of Qatar that aims to recruit and follow up for 5 years a sample of 3000 pregnant women and their children from birth to childhood. The main objectives of the cohort are briefly cited below:To evaluate maternal health pre- and postnatally including gestational diabetes, metabolic syndrome, obesity and postpartum depressionTo identify gene-environmental interaction affecting fetal growth and child healthTo assess the prevalence of nutritional, environmental, biological, and psychosocial exposures in the prenatal period and early childhoodTo examine the impact of these exposures on health-related outcomes such as birth outcomes, neurodevelopment, obesity, asthma and allergies that appear in early life and is likely to perpetuate into late childhood or adulthoodTo apply new innovative technology platforms "omics" to transfer knowledge from bench side to population sideTo provide valuable evidence-based data to policy makers so as to design effective policies that improve health

This is a multidisciplinary five year cohort study that is developed by the Ministry of Public Health in Qatar (MOPH-Q) in collaboration with various national research institutions, such as Primary Health Care Centers, Qatar University, Weill Cornell Medical Center-Q, Qatar Biomedical Research Institute, Qatar BioBank, Qatar Environmental and Energy Research Institute, Texas A & M University-Q, Sidra Medical Center, Hamad Medical Corporations, and international collaboration with the Barcelona Institute for Global Health (ISGlobal) in Spain.

### Ethical approval

The MOPH-Q has provided local Institutional Review Boards (IRBs) with national guidelines for overseeing research studies that involve vulnerable subjects such as pregnant women and children in order to maintain the safety and wellbeing of these participants. Large cohorts that involve collection of biological samples and handle genetic information present emerging ethical and legal issues including, but not limited to, privacy, psychological, legal, social, consent, etc. Many of these risks involve the potential for a breach of confidential information. Therefore, decreasing the risks of a breach of confidentiality reduces the risk of subsequent psychological, privacy, legal, and social harms. In order to mitigate those risks while conducting this cohort study, three main approaches are currently in place to secure collected information: 1- physical procedures that include locked cabinets, locked offices, and housing of database servers in rooms with tightly controlled access. 2- Technical procedures that include password protection, encryption, and firewalls. These procedures are designed to limit access to confidential information to those individuals or computer programs that have been granted access rights. 3- Administrative procedures such as procedures for training research staff, confidentiality agreements, and certificates of confidentiality. In addition, continuous training sessions is provided to the research team ensuring that every step in participation is understood (e.g., translating documents to appropriate languages). Trained staff assesses the informed consent and make sure that the participants have understood the purpose of the study, including the duration of participation, procedures/methods, risks and benefits, and the terms of confidentiality. It is clearly stated within the consent form and the information flyer that their participation is voluntary at every point in the project.

The study has been reviewed and ethically approved by the Institutional Review Board (IRB) of the Qatar BioBank Ethics Committee (Protocol ID: Full Board/2017/RES-ACC-0067/0019).

### Study population

Eligible participants for this study are all pregnant women who have lived in Doha for at least 15 years, and will give birth in Qatar within the 2 year period (anticipated number: 3000 families) of recruitment along with their husbands. This is the first phase of the study where the pregnant Qatari women and their husbands are being contacted before the 15th week of gestation at the Primary Health Care Centers (PHCC) in Doha, Qatar. Study participants need to be residents in the study area, older than 16 years, with no communication handicap. The consented participants are interviewed to obtain information on several sociodemographic and lifestyle factors and maternal characteristics are assessed based on anthropometric measurements, spirometry, blood pressure and other clinical measurements. Pregnant women are invited to provide blood, urine, saliva, hair and feces samples throughout their pregnancy, as well as cord blood and tissue, placental tissue, colostrum and breast milk at delivery, according to the scheduled visits (Fig. 1).

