Birth		Clinical records: induced abortion fetal or perinatal loss, caesarean	Sex, weight, length, HC, AC, Apgar score	Cord blood Cord tissue Placenta Meconium Colostrum Breast milk Hair

*Abbreviations*: *FFQ* Food Frequency Questionnaire, *CRL* Crown-rump length, *HC* head circumference, *BPD* biparietal diameter, *FL* femur length, *AC* Abdominal circumference

During the third trimester, pregnant women will be approached again for a follow up visit similar to the first one where maternal stress will be also assessed via questionnaire. Pregnancy-related complications and fetal ultrasound measurements will be obtained by the medical records of the participants. At birth, research assistants will clinically examine the infant (weight, length, anogenital distance, head circumference) and collect information on the type of delivery, infant sex and gestational age. Pregnant women will be invited to provide blood and urine samples at the scheduled visits during pregnancy, as well as cord blood and colostrum at delivery. Fathers who accompany their wife will also be invited to participate in the study. Once they agree they will be invited for a visit at Qatar Biobank where they will be informed about the study by trained personnel. Consented participants will be asked to complete a face to face questionnaire regarding their lifestyle and medical history and to provide biological samples (Blood, urine, saliva, feces and semen). All clinical visits of the participants will be located at Qatar Biobank.

The biochemical profile of the pregnant women, their husbands and their children will be assessed including total cholesterol, high-density lipoprotein (HDL), low-density lipoprotein (LDL), glucose, insulin, thyroid hormones and antibodies, leptin, adiponectin, C - reactive protein (CRP), inflammatory biomarkers. ‘Omic’ analyses will be conducted in mothers, fathers and children with main focus on the identification of early markers of maternal health effects and reproductive outcomes and on the evaluation of gene-environment interactions.

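### Eligibility rests on giving birth in Qatar within the 2-year recruitment period, a fact unknown at contact before week 15; as written it conflicts with the plan to study abortion and early loss

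*Protocol article*

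**What the plan says.** The formal criterion is in the Study population section of the protocol article: women who have lived in Doha for at least 15 years and who "will give birth in Qatar within the 2 year period (anticipated number: 3000 families) of recruitment along with their husbands". The next sentence says that the women and their husbands "are being contacted before the 15th week of gestation at the Primary Health Care Centers (PHCC) in Doha, Qatar". The abstract uses the same two years and the same count for enrolment: "recruitment phase of the study (duration: 2 years; expected number: 3000 families".

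On pregnancy loss, the Background says that the study "will investigate the increasing stillbirth rates [16, 17] and the concern of high abortion". The Birth row of Table 1 (Recruitment and data collection) lists "induced abortion fetal or perinatal loss" among the clinical records to be obtained. The Methods/design section sets a 5-year follow-up of 3000 pregnant women and their children, and names birth outcomes among the objectives.

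**The concern.** A cohort that enrols in early pregnancy should define membership by what is known on the day of enrolment. This criterion uses two later facts: that the pregnancy ends in a birth, and that the birth falls before recruitment closes. Three things follow if an analyst applies it as written.

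- Pregnancies ending in abortion or early loss fail the rule, so they leave both the numerator and the denominator. The abortion risk among eligible women would be zero by definition, although abortion is a named research question.
- One two-year window cannot serve both as the enrolment period and as the limit for delivery, because each delivery comes about half a year after enrolment.
- Near the end of the window, eligibility depends on length of gestation, which is itself a birth outcome.

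The Discussion names selection bias at recruitment as a major concern, and this rule is a source of it that the authors control.

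**Working it through.** **Inputs from the article.** Recruitment lasts 2 years (taken as 104 weeks) with 3000 families anticipated. Contact is before week 15, and the first assessment in Table 1 is at 12–15 weeks. The Background gives a preterm rate of 8.5%.

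**Assumed, because the article does not give them.** Birth at 38–40 weeks, the shape of accrual, and the gestational age of preterm births.

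**The plan's own figure.** 3000 over 24 months is 125 per month. No birth rate, participation rate or precision target is given, so the 3000 cannot be reproduced from the text.

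**1. Pregnancy losses, text against text.** Study population requires a birth. The Background and the Birth row of Table 1 treat abortion and fetal loss as outcomes to be studied and recorded. A pregnancy ending in abortion or early loss cannot satisfy the first and is needed for the other two. A stillborn delivery can be read as giving birth, so the firm contradiction covers abortion and early loss.

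**2. Recruits delivering after the window, uniform accrual.** Share = (gestation at birth − gestation at entry) / 104.

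| Entry (weeks) | Birth at 38 weeks | Birth at 40 weeks |
|---|---|---|
| 12 | 26/104 = 25.0% (750 of 3000) | 28/104 = 26.9% (808) |
| 13.5 | 24.5/104 = 23.6% (707) | 26.5/104 = 25.5% (764) |
| 15 | 23/104 = 22.1% (663) | 25/104 = 24.0% (721) |

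The range is about 22–27%, or about 660–810 of 3000. To keep 3000 under the literal rule, enrolment would have to reach 3000/(1 − 0.221) ≈ 3850 up to 3000/(1 − 0.269) ≈ 4100.

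**3. Other accrual shapes.** Take entry at 13.5 weeks and birth at 39.5, so d = 26/104 = 0.25.

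- Accrual falling linearly to zero: d² = 0.0625, about 6%.
- Accrual rising linearly from zero: 1 − (1 − d)² = 0.4375, about 44%.

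**4. Rule judged by expected delivery date.** With entry at 13.5 weeks and a date at 40 weeks, the last eligible enrolment falls at week 104 − 26.5 = 77.5. That is 77.5/104 × 24 ≈ 17.9 months. Reaching 3000 then needs 3000/17.9 ≈ 168 women per month instead of 125.

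**5. Tilt toward preterm birth, rule judged by actual delivery.** The chance of being kept is k = 1 − (gestation at birth − gestation at entry)/104. The preterm share among those kept is 0.085·k_p / (0.085·k_p + 0.915·k_t), where p is preterm and t is term.

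- Entry at 13.5, preterm birth at 35, term birth at 39.5: k_p = 1 − 21.5/104 = 0.793 and k_t = 1 − 26/104 = 0.750. The share is 0.0674/(0.0674 + 0.6863) = 8.9%.
- Extreme case, entry at 12, every preterm birth at 28, term birth at 40: k_p = 1 − 16/104 = 0.846 and k_t = 1 − 28/104 = 0.731. The share is 0.0719/(0.0719 + 0.6687) = 9.7%.

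The rise from 8.5% is about 0.4 percentage points, and 1.2 in the extreme case.

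**The case against.** The strongest reply is that the article contains no removal rule. A recruiter at the health centre can only apply the clause as an expectation of delivery in Qatar. Table 1 plans to record losses, so women with losses are evidently meant to stay. The article is also a condensed account, and rules for closing enrolment may stand in the full protocol. Much of this is right, and it limits what can be claimed.

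- A reader might infer that the study drops pregnancy losses and discards a quarter of its recruits. The documents do not support that: no section says that an enrolled woman is removed after a loss or a late delivery.
- A reader might infer that 3000 will not be reached. In the Study population sentence the 3000 stands next to the birth condition and can be read as the number already meeting it; subtracting 660–810 would then apply the condition twice.
- A reader might infer a serious excess of preterm births, since among women enrolled very late only early deliveries qualify. Few women are involved. With entry at 13.5 weeks, only preterm births qualify in the last 37 − 13.5 = 23.5 weeks. With 0.085 × 3000 = 255 preterm births, all at 35 weeks, 255 × (37 − 35)/104 ≈ 5 women enter this way. With all at 28 weeks it is 255 × 9/104 ≈ 22.

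What the reply does not remove is the criterion itself. It is stated, not left to another document, and it disagrees with the Background and Table 1. Reading it as an expected date removes the preterm tilt, but shortens enrolment to about 18 of the 24 months, and the article says nothing of that.

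**Conclusion.** The point holds as a badly fixed eligibility rule. It conditions entry before week 15 on a later event and, as written, contradicts the stated intention to study and record abortion and early loss. That contradiction rests on the text alone and carries the point.

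The timing problem is real, but its size depends on accrual. The figure of about a quarter needs enrolment at an even rate to the last day and a literal test on actual delivery; neither is stated, and other accrual shapes move the figure widely. The preterm tilt is in the expected direction, small under plausible gestational ages, and only a supporting argument. All of these sizes describe what the literal rule would do, not a procedure that the article sets out.

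**What to change.** Rewrite the eligibility sentence in Study population around facts known at contact: gestation below 15 weeks, the existing residence requirement, intention to deliver in Qatar, and an enrolment date within the 2-year window. Add that every enrolled pregnancy is followed to its outcome and kept in the analysis, including losses and births after recruitment closes. State that the 3000 are counted at enrolment.

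The change takes two or three sentences. Its downside is that outcome collection must run about 6 to 7 months past the last enrolment (28 weeks is about 6.5 months). The planned 5-year follow-up already covers that time.

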**Fig. 1 Fig1:**
[figure not shown]
QBiC follow-up visits during pregnancy

### Recruitment and data collection

Research assistants contact pregnant women at the PHCC during their first scheduled major ultrasound test, and kindly invite them to participate in the QBiC study. Those interested to participate are scheduled for a visit at Qatar Biobank where they have the opportunity to discuss the study in depth with a research member and provide a written consent form. Consented participants, are invited to complete a baseline questionnaire, via face to face interview, including sociodemographic and lifestyle characteristics, and environmental exposures. Table 1 provides an overview of assessments and data that are collected at recruitment phase up to delivery for the pregnant women, the fathers and the fetus. Dietary habits of the women are assessed with the use of a food frequency questionnaire (FFQ) and 24-h recalls. Research assistants also assess anthropometric measurements of the participants including height, weight, waist circumference and hip circumference, bio-impedance analysis, cognitive function test, grip strength, vision, cardiovascular system (i.e. blood pressure, electrocardiogram, arterial stiffness, carotid ultrasound), respiratory function (by spirometry) and fetus ultrasound measurements.

**Table 1 Tab1:** Data planned to be collected at recruitment phase up to delivery

Follow-up	Questionnaires	Clinical examination	Ultrasound measurements	Biological samples
Mother				
12–15 weeks	General FFQ 24 h recall	Anthropometric characteristics Skinfolds Bioimpedance SCORAD test Metabolic syndrome Blood pressure Spirometry Thyroid malfunction Gestational diabetes	Placental function: resistance indices of the uterine and umbilical arteries	Blood Urine Saliva Feces
32 weeks	General FFQ 24 h recall	Anthropometric characteristics Bioimpedance Skinfolds Blood pressure Spirometry Thyroid malfunction Gestational diabetes	Placental function: resistance indices of the uterine and umbilical arteries	Blood Urine Saliva Feces
Delivery	Psychological	Gestational diabetes, preeclampsia, hypertension		
Father				
1st Visit	General	Anthropometric characteristics Bioimpedance Skinfolds Blood pressure		Blood Urine Saliva Feces Semen
Fetus				
12–15 weeks			CRL, HC, BPD, FL, AC	
32 weeks			HC, BPD, FL, AC Organ development: brain, heart, kidneys, blood flow	
Birth		Clinical records: induced abortion fetal or perinatal loss, caesarean	Sex, weight, length, HC, AC, Apgar score	Cord blood Cord tissue Placenta Meconium Colostrum Breast milk Hair

*Abbreviations*: *FFQ* Food Frequency Questionnaire, *CRL* Crown-rump length, *HC* head circumference, *BPD* biparietal diameter, *FL* femur length, *AC* Abdominal circumference

During the third trimester, pregnant women will be approached again for a follow up visit similar to the first one where maternal stress will be also assessed via questionnaire. Pregnancy-related complications and fetal ultrasound measurements will be obtained by the medical records of the participants. At birth, research assistants will clinically examine the infant (weight, length, anogenital distance, head circumference) and collect information on the type of delivery, infant sex and gestational age. Pregnant women will be invited to provide blood and urine samples at the scheduled visits during pregnancy, as well as cord blood and colostrum at delivery. Fathers who accompany their wife will also be invited to participate in the study. Once they agree they will be invited for a visit at Qatar Biobank where they will be informed about the study by trained personnel. Consented participants will be asked to complete a face to face questionnaire regarding their lifestyle and medical history and to provide biological samples (Blood, urine, saliva, feces and semen). All clinical visits of the participants will be located at Qatar Biobank.

The biochemical profile of the pregnant women, their husbands and their children will be assessed including total cholesterol, high-density lipoprotein (HDL), low-density lipoprotein (LDL), glucose, insulin, thyroid hormones and antibodies, leptin, adiponectin, C - reactive protein (CRP), inflammatory biomarkers. ‘Omic’ analyses will be conducted in mothers, fathers and children with main focus on the identification of early markers of maternal health effects and reproductive outcomes and on the evaluation of gene-environment interactions.

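### The only described invitation route for fathers depends on accompanying the wife, so planned paternal data would be filtered by attendance before consent

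*Protocol article*

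**What the plan says.** The article describes the approach to fathers in three places.

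- **Abstract and Study population.** Both present contact as made with the couple. In Study population, "the pregnant Qatari women and their husbands are being contacted before the 15th week of gestation at the Primary Health Care Centers". That section also includes husbands alongside the women in its eligibility statement and gives the size as "anticipated number: 3000 families". The abstract has "expected number: 3000 families".
- **Recruitment and data collection, opening.** Only the women are named at first contact: "Research assistants contact pregnant women at the PHCC during their first scheduled major ultrasound test".
- **Recruitment and data collection, after Table 1.** The father's route is given as "Fathers who accompany their wife will also be invited to participate in the study". Those who agree then have a separate Qatar Biobank visit, where they are informed, asked to consent, interviewed and sampled (blood, urine, saliva, feces and semen).

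The same section plans biochemical profiles and omic analyses in fathers as well as in mothers and children, with gene-environment interaction among the aims. The opening of Methods/design states the size without fathers: the study "aims to recruit and follow up for 5 years a sample of 3000 pregnant women and their children from birth to childhood".

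**The concern.** The eligibility text covers all husbands of eligible women, but the operating rule reaches only those who come along. No route is described for a husband who does not come. His absence would therefore be decided by the recruitment procedure and not by his own refusal.

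This matters if coming along is related to what the study measures. Work, social position, or an earlier pregnancy loss could each affect whether a husband attends. Social factors, abortion and stillbirth are all named as study interests in the Background. An association between paternal characteristics and outcome, estimated only in families where the father attended, could then differ from the association among all enrolled families.

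If attendance and invitation are not recorded, a father who was never asked cannot be told apart from one who declined, and the selection could not be described afterwards.

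**Working it through.** The plan has no figure to reproduce. The 3000 is an expected recruitment number over 2 years, given without a sample-size calculation, and no number of fathers is stated. The check is therefore a comparison of the texts plus one line of illustrative arithmetic.

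**1. Who is approached**

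| Place | Who is approached | Condition |
|---|---|---|
| Abstract; Study population | Women and husbands, at the health centers | Before week 15; no attendance condition |
| Recruitment and data collection, opening | Women | First major ultrasound |
| Recruitment and data collection, after Table 1 | Fathers | Accompanying the wife |

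The last row is narrower than the first. The two can be read together only if the first row is taken to mean husbands who are present at the health center. On that reading attendance is still the filter.

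**2. Steps before a father contributes data**

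He accompanies, is invited, agrees, attends a separate visit, consents, and gives samples. Refusal at the later steps is unavoidable in any cohort. The attendance step is a choice of procedure.

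**3. Existing safeguards**

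The Discussion recognises selection at recruitment and calls for regular comparison of participants with non-participants. It does not name fathers, and a comparison describes a filter without removing it. Statistical considerations discusses imputation for mother-child pairs, not for missing fathers.

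**4. What the 3000 counts**

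Methods/design equates it with women and their children. No section makes an enrolled father a condition for counting a family.

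**5. Illustration**

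Let f be the share of enrolled women whose husband accompanies her and consents. The documents give no value for f, so these values are assumptions.

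Families with father data = 3000 × f

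- f = 0.3: 3000 × 0.3 = 900
- f = 0.5: 3000 × 0.5 = 1500
- f = 0.7: 3000 × 0.7 = 2100
- f = 0.9: 3000 × 0.9 = 2700
- f = 1.0: 3000 × 1.0 = 3000

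The recruitment target for women and their children is 3000 in every row. The arithmetic shows only that the amount of father data depends on a rate that the article does not state. It says nothing about the direction or size of any bias.

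**The case against.** **The conflict is mild.** The article does not say that only accompanying fathers are invited, and it excludes no other route. The abstract also says that fathers are asked for samples. A journal article condenses a fuller protocol, which may describe how absent husbands are reached. This stands in part: it cannot be concluded that absent husbands are never asked. But the one route that is described carries a condition which the eligibility text lacks, and that is a matter of stated wording.

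**The bias is conjecture.** No evidence is given that attendance depends on anything under study. If attendance is judged at first contact, before week 15, complications arising later cannot have caused it. This also stands as far as it goes. It leaves social circumstances and earlier losses as possible shared causes, and the sentence on accompanying fathers does not say which appointment is meant.

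**Fathers are secondary in a mother-child cohort.** None of the listed objectives names them. That limits the reach of the point. It does not remove it, because father samples and father omic analyses are planned.

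**The count.** A reader might infer that 3000 families is an overstatement, since fewer than 3000 mother-father-child sets would result. The documents do not support this. The number is an expectation, Methods/design gives it as women and their children, and no target for fathers is set. Any specific shortfall would rest wholly on assumed attendance and consent rates.

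**Analysis remedies.** Weighting for father participation is commonly left to the statistical analysis plan, so its absence here is not a finding.

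**Conclusion.** The point holds as an inconsistency in how fathers are approached, with an avoidable selection step for the paternal data. As written, those data would come from fathers filtered by attendance before consent, and the general participant/non-participant comparison in the Discussion does not remove that filter. This rests on following the described procedure literally, with no further route for absent husbands. That attendance is related to exposures or outcomes is plausible reasoning, not something the documents show, so no size can be put on any bias.

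The consequence is confined to analyses that use father data. Mother-child analyses and their target of 3000 stand. The change is worth making because it is cheap and because fathers missed early in pregnancy cannot be approached at that stage later.

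**What to change.** 1. Reconcile the abstract, Study population and both parts of Recruitment and data collection. State that the husband of every enrolled woman is invited through her, by a take-home invitation or a call, whether or not he accompanies her.
2. Record for each enrolled woman whether her husband accompanied her, was invited, and accepted or declined.
3. State that 3000 refers to mother-child pairs, and report the number of families with father data separately.
4. Compare families with and without father data on the maternal baseline information already collected at enrolment.

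The cost is one invitation and one status field per woman, plus a descriptive comparison using data already held. Whether to weight the paternal analyses for participation can be left to the statistical analysis plan; the status field and the maternal baseline data would make it possible.
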